#### Implementation/Fidelity

Home visiting interventions involve three components: Dose (timing/length of visits); Content (degree to which it was delivered); and Rapport (quality of visitor-participant relationship) [74]. To assess Dose and Content**,** we will adapt a home visit form used in large home visiting studies, for CHALO [75] (see Additional file 1: Figure S1) to be completed after each visit. To assess relationship warmth and rapport, both CHWs and mothers will complete the Working Alliance Questionnaire [76] adapted for the study.

#### Recruitment and retention

Practices will generate quarterly lists of 2–5 month olds seen for well-child visits. Parents will receive an “opt-out” letter from the pediatrician when their child is 4–5 months old, with a number to call to decline study contact. Parents who do not decline will be contacted by study staff to arrange a Baseline (T0) interview. We will set individual practice target recruitment rates based on target population size at each practice. Strategies to promote retention include: gift card incentives for research interviews, quarterly post-card reminders and incentives to notify study of address or name changes, holiday greeting postcards, and reminders for upcoming interviews.

#### Randomization and masking

Participants will be randomized 1:1 to the intervention or EUC control group, after providing informed consent (see below). Following delivery of the EUC at the T0 (baseline) assessment, the CHW will randomize participants by opening a sealed envelope containing the random assignment (prepared in advance by the project statistician). This sequence preserves masking of outcomes assessment at the T0 interview. Neither the outcomes section of the study database, nor written study materials will include a group identifier, though participants may indicate group assignment to research assistants at the12-month (T1) and 18-month (T2) follow-ups.

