#### Enhanced usual care (control)

An EUC counseling intervention will be delivered immediately following the T0 Baseline Interview, just prior to randomization. EUC Components include: 1) a pamphlet- containing basic ECC and Obesity prevention messages, and 2) Dental Referrals. We developed a Screened Dental Provider list of dentists who: a) are willing to see 12 month old children; and b) accept most insurance plans in the study practices.

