#### Intervention

CHWs will conduct *n* = 6 home visits when the child is 6, 8, 10, 12, 14, and 16 months old. Of these, 4 visits include only the mother-child dyad. Visits at 8 and 14 months will include a senior family decision maker (e.g., husband or mother-in-law). CHWs will conduct 6 follow up telephone calls in alternate months. Calls will be used to ask about the family’s goals for change, gauge progress, and assist with trouble shooting.

*Mother-only visits* will focus on building rapport and intimacy, identifying family/household concerns, reviewing risk/health behaviors, reviewing, setting, and troubleshooting goals, building skills through active interaction with the child, and providing education. Messages will be provided orally and via culturally tailored, attractive educational materials. To bolster mothers’ skills, CHW-guided interactions with the dyads will include: recognizing infant satiety and hunger cues via responsive bottle feeding, preparing age-appropriate self-feeding foods, encouraging tummy time and active play, transitioning from naptime milk to water bottles, and oral hygiene practices such as tooth brushing. At each visit, the CHW encourages the mother to set a concrete, manageable behavior change goal. Patient navigation, as needed, will encourage mothers to make and keep two dental visits for their child, over the 12 month follow-up. *Family visits* will, similarly, assess family views on barriers to change, and enlist support for mothers’ child feeding goals (Fig. 1).

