#### Human subjects

This study was approved by the Albert Einstein college of Medicine’s Committee on Clinical Investigation. Bi-lingual research assistants will consent mothers in their home prior to the baseline (T0) interview.

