#### Data management

We will use REDCap (Research Electronic Data Capture) software for database development, data entry, coding and secure data storage [80]. Research assistants can access REDCap both onsite and in the field, and enter data directly as it is collected. The team will use REDCap features to manage follow-up reminders, and adherence to T1 and T2 windows for interview completion. All data will be maintained in secure files during and after the trial.

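### The community health worker, whose role delivers the intervention, also opens the envelope that assigns the arm; independent, time-stamped release would close a modest but avoidable gap in allocation concealment

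*Protocol article*

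**What the plan says.** The Randomization and masking section states that "Participants will be randomized 1:1 to the intervention or EUC control group, after providing informed consent". Once EUC has been given at baseline, "the CHW will randomize participants by opening a sealed envelope containing the random assignment"; the assignments are "prepared in advance by the project statistician". The only reason offered for this order of steps is that it keeps the T0 assessment masked.

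The Intervention section gives delivery to the same role: "CHWs will conduct *n* = 6 home visits when the child is 6, 8, 10, 12, 14, and 16 months old", plus six telephone calls.

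On sequence and setting, the Enhanced usual care section says that "An EUC counseling intervention will be delivered immediately following the T0 Baseline Interview, just prior to randomization", Table 2 places the T0 interview in the home, and the Human subjects section says that "Bi-lingual research assistants will consent mothers in their home prior to the baseline (T0) interview". The Data management section adds that "Research assistants can access REDCap both onsite and in the field, and enter data directly as it is collected".

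**The concern.** Allocation concealment is safest when the person who reveals the assignment has no part in delivering the treatment. Here the CHW role has a possible stake. Families assigned to the intervention become its workload. The Implementation/Fidelity section measures the dose, content and rapport of its visits. In the later outreach phase, CHWs recommend intervention mothers for groups that CHWs lead. None of this implies misconduct. It explains why the step is better placed elsewhere.

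The T0 masking rationale protects the baseline measurement, and only if the envelope has not been read beforehand. It does not stop an envelope being swapped or taken out of order for a family that has just shown how receptive it is.

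Allocation matters more than usual in this trial. The primary outcome is a daily count of bottles and sippy cups taken from the mother's recall. Mothers know their arm, and the article accepts that they may reveal it to research assistants at T1 and T2. Sound allocation is one of the few bias protections left.

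**Working it through.** **Who does what, in order**

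| Step | Role | Where stated |
|---|---|---|
| Assignments prepared | Project statistician | Randomization and masking |
| Consent, in the home | Research assistants | Human subjects |
| T0 interview, in the home | Role not named in the table | Table 2 |
| EUC, straight after T0 and before randomisation | Role not named | Enhanced usual care (control) |
| Envelope opened | CHW | Randomization and masking |
| Six home visits and six calls | CHW | Intervention |
| T1 and T2 contact | Research assistants | Outcomes measurement; Randomization and masking |

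That the envelope is opened in the home is an inference from the setting of consent and T0 and from the immediate succession of steps. It is a strong inference, but the article does not state it.

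Consent, T0 and EUC all precede opening, and consent belongs to another role. Selective enrolment would therefore require an envelope to be read in advance. The main exposure left is steering the assignment of a family already enrolled.

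**The plan's own figure.** The Sample size section gives a difference in decline of 0.7, a divisor of 2 (hence d = 0.35), 150 per arm and two-sided alpha 0.05, with power above 85%.

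- 0.35 × √(150/2) = 3.03
- 3.03 − 1.96 = 1.07, and Φ(1.07) = 0.858
- A noncentral t calculation with 298 df gives 0.856.

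The stated power reproduces and is not in dispute here. It supplies the 0.7 and the 2 used below.

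**Illustration of the bias.** The steering fraction and the family difference are assumptions; the article gives neither.

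- Families steered: 5% of 360 = 18, taken as 9 receptive families directed to intervention and 9 unreceptive families directed to control.
- Under 1:1 allocation about half would have reached that arm anyway, so about 9 are actually moved, 4.5 each way.
- Assumed difference between receptive and unreceptive families in later change: 2 bottles a day.
- Shift per arm: 4.5 × 2 / 180 = 0.05, in opposite directions.
- Between-arm bias: 0.05 + 0.05 = 0.1 a day; 0.1 / 0.7 = 14%.

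In general, with steered fraction f and difference in change D, each arm shifts by (f × 360 / 4) × D / 180 = f × D / 2, so the bias is f × D:

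| f | D (bottles/day, in change) | Bias | Share of 0.7 |
|---|---|---|---|
| 2% | 2 | 0.04 | 6% |
| 5% | 1 | 0.05 | 7% |
| 5% | 2 | 0.10 | 14% |
| 10% | 2 | 0.20 | 29% |

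**Why the difference must be in change.** The primary test is the arm-by-time interaction in a model with a person-level random intercept, and T0 is measured before allocation. A stable difference in level between families is present at T0 as well as later, so it largely drops out of that contrast. Only a difference in later trajectory carries through. The figures are on the mean scale of the sample-size calculation; the planned model reports a rate ratio.

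**The case against.** The strongest defence is that the article already separates much of the process. The CHW neither generates the sequence nor takes consent, and baseline data collection and EUC are finished before the envelope is opened. This stands, and it confines the concern to assignment of enrolled families.

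Four stronger readings are tempting but not supported:

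- **CHWs keep the envelopes.** The article says who opens them, not who stores or carries them.
- **Nothing is numbered, opaque or logged.** The article is silent on these details, but a journal article commonly leaves them to the full protocol. The silence is no defect.
- **The bias could exceed a quarter of the planned effect with 5% of families steered.** With D = 2, a shift of 0.2 (29%) needs 18 families whose arm is truly reversed. Under 1:1 allocation that means about 36 targeted, or 10%. It also needs the difference to lie in later change.
- **A ready electronic alternative is already in place.** The Data management section gives field access to REDCap to research assistants. It mentions neither CHW access nor a randomisation function, so REDCap is a feasible route and no more.

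The defence also raises a fair point about the remedy. If the assignment appeared on a research assistant's device, a later outcome assessor could learn the arm. The article tries to limit this by keeping group identifiers out of the outcomes section of the database and out of written materials.

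**Conclusion.** The concern holds as a stated design choice with a recognised weakness: the role that delivers the intervention reveals the assignment, and the rationale given does not cover early reading, swapping or reordering. The remaining risk is mainly at assignment of enrolled families, not at enrolment.

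Its size cannot be derived from the article. Under the assumed 5% steering and a difference of 2 bottles a day in later change, the bias is about 0.1 a day, 14% of the planned 0.7. The other assumed values shown give 6% to 29%. If steered families differed only in stable level, little bias would reach the interaction estimate. Differences in unmeasured receptiveness that affect later change could not be adjusted away. The article gives no ground for saying that subversion would occur. The change is a cheap improvement worth making, not a correction on which the trial's validity depends.

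**What to change.** Replace envelope opening by the CHW with central or electronic release of the statistician's list, for example through a REDCap randomisation function or a call-in service. Issue each assignment, with a timestamp, only after the T0 record is saved and EUC is recorded as delivered. Show it to the CHW but not to the research assistants who assess T1 and T2. Keep sealed envelopes only as a backup for lost connectivity, held by someone outside the CHW team.

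The cost is software set-up, CHW access to the release system, a data connection or telephone call at the visit, and a short procedure change. The order of steps, the sample size and the analysis model stay as they are.

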#### Human subjects

This study was approved by the Albert Einstein college of Medicine’s Committee on Clinical Investigation. Bi-lingual research assistants will consent mothers in their home prior to the baseline (T0) interview.

#### Sample size

Based on preliminary studies, we estimate a between group difference in decline in the number of daily bottles and sippy cups (combined) of 0.7. This equates to a small-moderate standardized effect size (Cohen’s d) of 0.7/2 = 0.35. With *n* = 300 participants (150 per am) the trial will have greater than 85% power to detect an effect size of 0.35 (two-tailed alpha = 0.05)**.** To account for a 20% attrition rate, we will enroll 360 subjects (180 per arm).

Analysis plan: Analyses will be intent-to-treat. Generalized linear mixed models (GLMM) will be employed to analyze primary CRFA outcomes, as well as unique obesogenic and cariogenic outcomes. To test the impact of the intervention on secondary outcomes-- caries, weight for length, velocity of weight gain-- similar GLMM models will be fit. Individuals lost to follow-up at T1 or T2 will remain in the analytic sample. Further details are provided below.

The trial’s primary outcome is frequency of combined sippy cup and bottle use (count/day). The intervention’s effectiveness will be tested by a random-effects Poisson regression model, with the count of bottle/sippy cup as dependent variable, an indicator for study arm, a time indicator and their interaction term as fixed effects, and a random intercept at the person level. We will adjust for child age, given shifts in feeding behavior at this age. If the mean (sd) of the outcome demonstrates over -dispersion relative to a Poisson model, we will use negative binomial regression instead. We will report the coefficient of the interaction term, which estimates the rate ratio in bottle/sippy cup use attributable to the intervention, and its 95% confidence interval. To test the null hypothesis, we will use a z-test.

To test the impact of the intervention on secondary outcomes (behavioral), we will use random-effect generalized linear regression models. The intervention’s impact will be assessed by the coefficient of the interaction term. The estimate and its 95% confidence interval will be reported. For secondary caries, weight for length, and velocity of weight gain outcomes, logistic regression or a linear regression model will be applied as appropriate. *Anthropometrics*: We will use WHO growth standards [77] to calculate *BMI-for-age Z scores* --weight/length^2^ (kg/m^2^), standardized for sex and actual age at measurement. We will categorize children as “overweight” and “obese” if their BMI-for-age Z-scores exceed + 2 and + 3, respectively, as recommended by the WHO [78], and *Weight velocity Z scores*: for each 6 month period: 6 m. > 12 m. 12 m. > 18 m.

**Missing data** will arise from both non-response and study attrition. Random bias created by missing items will be addressed by using multiple imputations [79]. These will use chained equations incorporating baseline and end-of-study data and behavioral variables. For non-random bias, sensitivity analyses will be used to impute best and worst-case credible values for missing variables and then apply the original analyses to these supplemented data sets.

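### Minor arithmetic error in the sample size: 360 enrolled keeps 150 per arm only up to 16.7% attrition, not the stated 20%

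*Protocol article*

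**What the plan says.** The Sample size section of the protocol article sets out a two-group calculation for the primary outcome, the daily count of bottles and sippy cups.

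- **Effect:** "we estimate a between group difference in decline in the number of daily bottles and sippy cups (combined) of 0.7", expressed as a "small-moderate standardized effect size (Cohen’s d) of 0.7/2 = 0.35". The division implies a standard deviation of 2.
- **Power:** for 300 participants, 150 per arm, "the trial will have greater than 85% power to detect an effect size of 0.35", with "two-tailed alpha = 0.05".
- **Attrition:** "To account for a 20% attrition rate, we will enroll 360 subjects (180 per arm").

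The Abstract repeats the enrolment figure of 360. Randomization and masking gives equal allocation: "Participants will be randomized 1:1 to the intervention or EUC control group". No other attrition rate appears in the article.

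The analysis plan in the same section keeps participants lost at the 12-month (T1) or 18-month (T2) assessment in the analysed sample. The paragraph on missing data plans multiple imputation by chained equations, with sensitivity analyses.

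**The concern.** The enrolment target is the completer target plus 20% of the completer target. Losses, however, are taken from those enrolled, so adding 20% does not offset losing 20%. The two adjacent statements, 300 for the power and 360 to cover the attrition, therefore do not join up at the stated rate.

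Two things are at stake, both modest. First, the margin above 85% power at 300 participants is under one percentage point, so even a small shortfall in completers takes the calculation below the stated level. Second, anyone who monitors retention against the 20% figure would believe that 300 completers are secured, when the real tolerance for 300 is lower.

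**Working it through.** **Inputs.** All come from the protocol article: difference 0.7 and SD 2 (d = 0.35), two-sided alpha 0.05, 150 per arm for the power statement, 20% attrition and 360 enrolled (Sample size); 1:1 allocation (Randomization and masking).

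**Step 1: reproduce the plan's power.** For n per arm, the normal approximation is

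power = Φ(d × √(n/2) − 1.960).

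With n = 150: 0.35 × √75 = 3.031; 3.031 − 1.960 = 1.071; Φ(1.071) = 85.8%. The two-sample t-test (noncentral t) gives 85.6%. The stated power of more than 85% at 300 participants is confirmed.

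**Step 2: reproduce the plan's enrolment figure.**

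- By multiplication: 300 × 1.20 = 360. This is the plan's number.
- By division: 300 / (1 − 0.20) = 375. By arm, 150/0.80 = 187.5, rounded up to 188, or 376 in total.

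Only the multiplicative form gives 360. The gap to 375 is 15 participants.

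**Step 3: what 360 delivers.**

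- At 20% attrition: 360 × 0.80 = 288, or 144 per arm. This is 12 fewer than 300.
- Attrition at which 300 remain: 1 − 300/360 = 16.7%.

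**Step 4: power at 144 per arm, same method, completers only.** 0.35 × √72 = 2.970; 2.970 − 1.960 = 1.010; Φ(1.010) = 84.4%. The t-test gives 84.1%.

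**Step 5: how far this is from 85%.**

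| Completers per arm | Normal approximation | t-test |
|---|---|---|
| 144 | 84.4% | 84.1% |
| 147 | 85.1% | 84.9% |
| 148 | 85.3% | 85.1% |
| 150 | 85.8% | 85.6% |

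The smallest arm that reaches 85% is 147 (normal) or 148 (t-test), that is 294 or 296 completers. At 144 per arm the calculation falls 0.6 to 0.9 points short of 85%, and about 1.4 points below its value at 150 per arm.

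**The case against.** The best defence has three parts.

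1. **The power claim is made for 300 participants, and it is right.** The article does not say in one sentence that 360 enrolled with 20% lost gives more than 85% power. This stands. The error lies only in the sentence that links 360 to 20% attrition; the lower power follows from reading the two sentences together.

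2. **The planned analysis is not a completers-only t-test.** It is a random-effects Poisson (or negative binomial) model over repeated assessments, which keeps participants lost to follow-up, and multiple imputation is planned as well. A child seen at T1 but lost by T2 still contributes. This stands in part: 84% is not shown to be the power of the planned model, and some of the small shortfall may be recovered. It does not rescue the 360. A child lost before T1 adds little to the arm-by-time interaction, and the article does not justify 360 by retained information. It inflates explicitly for attrition from a two-group calculation, and the inflation is wrong on those terms.

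3. **The effect is trivial next to the uncertainty in the inputs.** At 144 per arm, 85% power corresponds to d of about 0.353 to 0.354, which with an SD of 2 is a difference of about 0.71 a day instead of 0.70. The planning value is given to one decimal only. This stands, and it settles the severity.

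A reader might go further and infer that the trial is materially underpowered, or that the stated attrition and the stated power are strictly incompatible. The article does not support either reading. The shortfall is under one percentage point on a simplified calculation, and the planned model uses data that this calculation discards.

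**Conclusion.** The point holds as a minor arithmetic error. The 360 does not do what the article says it does: it covers attrition of up to 16.7%, not 20%, if 150 per arm are to remain. At 20% attrition the article's own calculation moves from just above 85% to about 84%.

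The attrition result is pure arithmetic and assumes only that the rate is a fraction of those enrolled. The power result also assumes equal losses in the two arms, d = 0.35 as stated, and a two-sample comparison of completers. Nothing in the design, the conduct or the inference depends on the correction.

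**What to change.** Restate the attrition sentence in one of two ways:

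- **Preferred, because it is arithmetic alone:** enrolment of 360 (180 per arm) allows for up to 16.7% attrition while keeping 150 per arm.
- **Alternative, if 20% is to stay as the planning rate:** with 360 enrolled and 20% attrition, 288 completers (144 per arm) give approximately 84% power for d = 0.35 at two-sided alpha 0.05 in a completers-only two-sample comparison. The sentence may add that the mixed model retains participants lost to follow-up.

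The cost is one sentence, and either the stated attrition allowance or the stated power becomes slightly less favourable. Enrolment need not rise to 375 or 376, because the gain would be less than two percentage points of power.

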**Methods:**

This two part project includes a randomized controlled trial, and a Knowledge Translation campaign. A randomized controlled trial will enroll *n* =  360 families from pediatric practices serving South Asians in the New York metro area. The intervention group will receive home visits by SA community health workers at 6, 8, 10, 12, 14, and 16 months of age. Controls will receive culturally tailored educational material. Primary outcomes-- cariogenic and obesogenic feeding practices at 6, 12, and 18 months-- will be assessed with the MySmileBuddy iPad based tool. Secondary outcomes include: oral hygiene practices, anthropometrics, and caries incidence at 18 months. A public education campaign will focus on both families and health care providers.

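### The primary model tests a difference in change from a pre-randomisation T0 count and so loses precision that a common T0 mean would recover

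*Protocol article*

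**What the plan says.** The Analysis plan paragraphs of the protocol article (under Sample size) give the primary model as a random-effects Poisson regression of the daily count, or negative binomial if there is over-dispersion. Its fixed effects are "an indicator for study arm, a time indicator and their interaction term as fixed effects", with "a random intercept at the person level". The effect to be reported and tested by a z-test is the interaction: "We will report the coefficient of the interaction term, which estimates the rate ratio in bottle/sippy cup use attributable to the intervention". The only further adjustment is for age: "We will adjust for child age, given shifts in feeding behavior at this age". No T0 count appears as a covariate, and the arms are not constrained to share a T0 mean.

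The abstract places the outcome assessments at three ages: "cariogenic and obesogenic feeding practices at 6, 12, and 18 months". Randomization and masking puts the first of these before allocation: "Following delivery of the EUC at the T0 (baseline) assessment, the CHW will randomize participants". The sample size rests on a "between group difference in decline in the number of daily bottles and sippy cups (combined) of 0.7", divided by an SD of 2.

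**The concern.** At T0 nobody has been allocated, so the true arm difference there is zero. A model with a free arm main effect estimates that difference anyway and subtracts it from the follow-up difference. The interaction is then a difference in change (on the log scale, a ratio of rate ratios) and carries the sampling noise of T0 in full. A model that treats T0 as a baseline uses the same data and gives a tighter estimate.

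The lower the correlation between T0 and follow-up, the larger the loss. A fairly low correlation is plausible here: the count comes from a 24-hour recall (repeated only in a subset, per Common risk factor feeding behaviors), the child goes from 6 to 18 months of age, and the article itself expects feeding to shift over this period. But the article gives no value, so the size of the loss can only be shown over a range. At stake is the width of the primary confidence interval and, on one reading of the planning SD, whether the planned test reaches the stated power.

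**Working it through.** **Inputs from the article (Sample size).** Difference 0.7; SD 2, not stated whether of change or of one visit; 150 per arm; two-sided alpha 0.05; power above 85%. **Assumed, because not given:** the correlation r between T0 and follow-up; for the Poisson model, also the visit means.

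**1. The plan's own figure.** d = 0.7/2 = 0.35. Power = Φ(0.35·√(150/2) − 1.96) = Φ(3.031 − 1.96) = Φ(1.071) = 0.858 (0.856 by noncentral t). The stated power reproduces.

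**2. Gaussian variance.** With variance s² at each visit, the variance terms are:
- difference in change: 2s²(1 − r)
- T0 used as baseline: s²(1 − r²)
- ratio: (1 − r²)/[2(1 − r)] = (1 + r)/2, so the saving is (1 − r)/2

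Generalised least squares with three visits, equal correlations and categorical time gives the same saving for the T2-versus-T0 contrast. The article does not fix the time coding, and this matters: for r from 0.2 to 0.5 the saving is 53% to 33% with a pre/post indicator and 46% to 27% with linear time.

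**3. The planned Poisson model.** These savings come from the likelihood information of the random-intercept Poisson model with categorical time and assumed means that fall over the visits:
- T0 mean 4: 33% at r = 0.20, 25% at 0.37, 20% at 0.51, 16% at 0.60
- T0 mean 2: 31% at r = 0.25, 23% at 0.43
- T0 mean 6: 30% at r = 0.27, 21% at 0.49, 13% at 0.69

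The saving is smaller than the Gaussian one because, with falling means, T0 is the least noisy visit on the log scale. A direct simulation at T0 mean 4 (300 children, 250 replicates, so itself noisy) gave 29%, 24% and 7% at r = 0.18, 0.38 and 0.59.

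**4. Power at 150 per arm (normal approximation, Gaussian case).**
- If SD 2 is the SD of change, the planned test uses 2 and the common-T0 model uses 2√((1 + r)/2). At r = 0.2 that is 1.549: Φ(0.7/1.549 × 8.660 − 1.96) = Φ(1.95) = 0.975.
- If SD 2 is a single-visit SD, the planned test uses 2√(2(1 − r)) and the common-T0 model uses 2√(1 − r²). At r = 0.3 these are 2.366 and 1.908: Φ(2.562 − 1.96) = 0.726 and Φ(3.177 − 1.96) = 0.888.

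| r | Variance saved | SD 2 = change: planned → common T0 | SD 2 = single visit: planned → common T0 |
|---|---|---|---|
| 0 | 50% | 0.858 → 0.990 | 0.573 → 0.858 |
| 0.2 | 40% | 0.858 → 0.975 | 0.669 → 0.872 |
| 0.3 | 35% | 0.858 → 0.964 | 0.726 → 0.888 |
| 0.5 | 25% | 0.858 → 0.938 | 0.858 → 0.938 |
| 0.8 | 10% | 0.858 → 0.892 | 0.998 → 0.999 |

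**The case against.** The strongest reply is that nothing here is invalid. Arm, time and their interaction with a random intercept is a standard model, and it tests the same quantity on which the trial was sized. That stands: the plan is internally consistent, and the estimate is neither biased nor tested at the wrong level. It does not answer the loss of precision, because the terms and the tested coefficient are stated choices, not detail left to an analysis plan.

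A second reply is that a free arm term protects against imbalance at T0, since a community health worker opens the envelope after the T0 interview. This is weak. Under randomisation any imbalance is chance, and a common T0 mean or a T0 covariate handles it more efficiently.

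Third, the size depends on a correlation that the article does not give, and the simple formula belongs to a Gaussian model. Both points stand, so any single percentage is conditional. Fourth, that T0 is among the responses is inferred. It is the natural reading: without T0 the interaction would compare only T1 with T2, which does not match a sample size built on decline.

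A reader might infer that the trial is underpowered by design. The article does not support that. The SD of 2 divides a difference in decline, so it reads most directly as an SD of change, and then the stated power holds at 150 per arm. A shortfall appears only if SD 2 is a single-visit SD and r is below about 0.5.

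**Conclusion.** The point holds as an avoidable loss of precision on the primary outcome. In the Gaussian case the variance of the effect estimate would be about (1 − r)/2 lower with a common T0 mean: from 50% at r = 0 to 10% at r = 0.8. In the planned Poisson model it would be about 33% to 20% lower for r of 0.2 to 0.5 at a T0 mean of 4. The correlation, the T0 mean and the falling visit means are all assumptions.

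The effect on power turns on an ambiguity in the article. With SD 2 as the SD of change, the stated power is met and the change only adds to it (about 0.94 to 0.975 for r of 0.5 to 0.2). With SD 2 as a single-visit SD, the planned test falls short of the stated level at r = 0.2 and 0.3, while the common-T0 model exceeds 85% at every r in the table. A flat claim that a quarter to two fifths of the variance is lost would go too far: it needs r between 0.5 and 0.2 and the Gaussian formula. The change is worth making but is not essential to the validity of the trial.

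**What to change.** Before unblinding, specify the primary model with categorical time, arm-by-T1 and arm-by-T2 terms, no arm main effect (so both arms share one T0 mean) and a person random intercept. State which of the two contrasts is the primary test.

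A separate but similar option is to model the T1 and T2 counts with a suitably transformed T0 count, for example log(count + 1), as a covariate. Under a log link the two are not equivalent, so one should be chosen in advance.

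Use the same approach for the behavioural secondary outcomes measured at T0, which are also to be judged by the interaction term. The gain for the binary ones was not computed here. Dental visits, asked about only at T1 and T2, are not affected. It would also help to say whether SD 2 refers to change or to one visit, and what r was assumed.

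The cost is a short change to the model specification. It needs no new data, no further participants and no change in conduct.
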